## Aims of the Study

The primary objective of Projecte Moviment is to examine the effect of CCT, AE, or COMB on cognitive outcomes in healthy physically inactive older adults. The primary hypotheses sustaining this goal are:

1.Computerized cognitive training – 5 times per week for 3 months – will improve general cognitive function as well as trained cognitive functions (executive function, processing speed and memory) measured by composite scores using a battery of validated neuropsychological tests at 3 months compared to a control group.2.Aerobic exercise – 5 times per week for 3 months – will improve executive function, attention-processing speed and memory measured by composite scores using a battery of validated neuropsychological tests at 3 months compared to a control group.3.Combined training – 5 times per week for 3 months – will show greater improvements in general cognitive function, executive function, attention-processing speed and memory measured by composite scores using a battery of validated neuropsychological tests at 3 months compared to a control group.

The secondary objectives of Projecte Moviment are: (a) to determine the effects of these interventions on psychological status and subjective performance on daily activities, CRF, brain structure and function and physiological molecular correlates; (b) to identify genetic, demographic, physiological and brain variables that might predict the effect of the intervention; (c) to identify the association between cognitive effects and other psychological, physiological correlates. Specific hypotheses for each objective will be specified in each article when reporting results. General secondary hypotheses include:

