Mini-Mental State Examination (MMSE)		X								X	
Geriatric Depression Scale (GDS-15)		X								X	
Medical history			X								
General health status			X						X		
Blood extraction			X						X		
Battery of neuropsychological tests				X						X^1^	
Psychological health and daily activities scales				X						X	
Physical activity questionnaire (VREM)				X						X	
Cardiorespiratory fitness (Rockport 1-mile walk test)				X						X	
Magnetic resonance imaging					X						X
Information about intervention						X					
Follow-up adherence questions^2^							X	X			
Actimeter^3^ (Polar Loop^®^)						X		X			
Intervention follow-up diary^4^						X	X	X			

*^1^All of tests except vocabulary subtest; ^2^This information is also collected in phone calls every 2 weeks between visits; ^3^Participants carry the actimeter the first and last week of training; ^4^Participants record the diary every day during the intervention; MoCA 5-min (Wong et al., 2015); MMSE (Blesa et al., 2001); GDS-15 (Martínez et al., 2002); VREM – Reduced Minnesota leisure time physical activity questionnaire (Ruiz et al., 2012); Rockport 1-mile walk test (Kline et al., 1987).*

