### Outcomes

#### Primary Outcomes

To address the primary hypothesis, an extensive neuropsychological battery was designed by Projecte Moviment. Each test has been selected for its psychometric qualities and high relevance in the area of study. These tests provide measures of multiple functions: executive functions, visuospatial abilities, memory, language, attention and processing speed. We will calculate z-score composites from normalized raw data for each cognitive domain and a global cognitive function score as a sum of all domains (Table 3).

**TABLE 3 T3:** Primary outcomes: variables and measures.

**Outcome/Variable**			**Outcome measure**
**Composites 1st level**	**Composites 2nd level**	**Tests – Subtest**	
**Executive function**	Inhibition	Stroop – Interference	*Z* score
	Working memory	WAIS III – Backward span	*Z* score
		TMT – B	*Z* score
	Fluency	Letter fluency	*Z* score
		Category fluency	*Z* score
**Visuospatial function**	Visuospatial	ROCF – Copy accuracy	*Z* score
**Memory**	Verbal memory	RAVLT – Total learning	*Z* score
		RAVLT – Recall II	*Z* score
	Visual memory	ROCF – Memory accuracy	*Z* score
**Language**	Language	WAIS III – Vocabulary	*Z* score
		BNT (15 items)	*Z* score
**Attention – Speed**	Attention	WAIS III – Forward span	*Z* score
		WAIS III – Digit symbol coding	*Z* score
		WAIS-III – Symbol search	*Z* score
	Speed	TMT – A	*Z* score
		ROCF – Copy time	*Z* score

*Stroop test (Golden, 2001); WAIS-III, Wechsler Adult Intelligence Scale (Wechsler, 2001); TMT, Trail Making Test (Tombaugh, 2004); Verbal fluency tests (Peña-Casanova et al., 2009); ROCF, Rey-Osterrieth Complex Figure (Rey, 2009); RAVLT, Rey Auditory Verbal Learning Test (Schmidt, 1996; Marqués et al., 2013); BNT, Boston Naming Test (Goodglass et al., 2001).*

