#### Statistical Analyses

Addressing the primary objective, statistical procedures will be performed with IBM SPSS Statistics 24 and R Environment. The distribution of raw scores will be examined in order to assess data quality (i.e., outliers, skewness) and we will obtain sample *z*-scores for all cognitive tests. Five primary domains will be calculated by adding *z*-scores – executive function, memory, language, attention-speed, and visuospatial function – which will be split into nine secondary domains in order to assess specific changes within each domain – inhibition, fluency, working memory, verbal memory, visual memory, language, attention, speed and visuospatial function (see Table 3). Domains will be based on the literature (Strauss and Spreen, 1998; Lezak et al., 2012) given the fact that a principle component analysis would not be appropriate for our sample size.

In order to test our primary hypotheses, we will conduct an intention-to-treat (ITT) analysis considering data from all randomized participants, including those that complete and drop-out, in order to prevent attrition bias. An adequate method of imputation will be applied and informed. Parametric or non-parametric tests will be chosen regarding the fitting of data to statistical requirements of the tests and we will follow a coherent pipeline to explore variance: (a) comparison of baseline values between groups to identify potential variables to adjust further analyses; (b) comparison of variables at different time-points for each group to identify the independent effect of each condition; (c) identification of significant cross-time correlations in order to determine whether it is necessary to control for baseline measures; (d) interaction between conditions and time-points to compare interventions. Sex, age, and years of education will be considered covariates beforehand and a two-tailed *p*-value < 0.05 will be set as the significant threshold and the corresponding correction for multiple comparisons will be applied. In a second phase, we will define a per-protocol (PP) sample including only subjects that finished the intervention with at least 80% adherence and we will reproduce the same pipeline. In case of high disparity between ITT and PP results, we will analyze potential variables related to that discrepancy.

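### Vocabulary belongs to the primary language and global scores but is not given at follow-up, so as written the two visits are scored from different tests

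*Protocol article*

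**What the plan says.** - **Composition.** Under Primary Outcomes, Table 3 gives the language domain two entries: "WAIS III – Vocabulary" and the 15-item BNT. The text there also defines "a global cognitive function score as a sum of all domains".
- **Scoring rule.** Statistical Analyses states: "Five primary domains will be calculated by adding *z*-scores – executive function, memory, language, attention-speed, and visuospatial function".
- **Schedule.** In Table 2 (Assessments), the post-intervention entry for the neuropsychological battery carries footnote 1: "All of tests except vocabulary subtest".
- **Analysis.** Step (b) of the pipeline is "comparison of variables at different time-points for each group to identify the independent effect of each condition". Step (d) is "interaction between conditions and time-points to compare interventions".
- **Hypotheses.** Under Aims of the Study, primary hypothesis 1 says that cognitive training "will improve general cognitive function as well as trained cognitive functions". Hypothesis 3 also names general cognitive function, for combined training. None of the three primary hypotheses names language.

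The article nowhere calls Vocabulary a baseline-only measure, and it defines no language or global score without it.

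**The concern.** The composite definition and the visit schedule cannot both be followed. If the domain is the sum of whatever listed tests are available, baseline language is Vocabulary plus BNT and follow-up language is BNT alone. The change is then the BNT change minus the person's baseline Vocabulary score. A participant 1 SD above the mean on both tests, with no true change, goes from 2 to 1 and appears to decline.

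Three things are at stake:
- the within-group comparison in step (b) for language, which is meant to show what each condition does by itself;
- the precision of the condition-by-time test in step (d), for language and to a lesser degree for the global score;
- any analysis relating cognitive change to baseline characteristics, because change would contain baseline Vocabulary with a minus sign.

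If the conflict stays open, the analyst can drop Vocabulary, carry it forward or sum unlike sets after the data are known.

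**Working it through.** The plan states no figure on this point, so there is none to reproduce. The check is a count from Table 3, then variances under stated assumptions.

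**Count (Table 3).** Executive function 5, visuospatial 1, memory 3, language 2, attention-speed 5: 5 + 1 + 3 + 2 + 5 = 16 tests. Without Vocabulary, 15. Vocabulary is 1/2 of language and 1/16 = 6.25% of a global score that sums all z-scores.

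**Assumptions (not in the documents).** Every z-score has variance 1 at both visits. The retest correlation is ρ = 0.8, with a range of 0.6 to 0.9 for language. Vocabulary correlates equally with each repeated test at both visits, so it is uncorrelated with their changes.

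**Language change.**
- BNT only: variance = 2(1 − ρ) = 2 × 0.2 = 0.4.
- As written: variance = 2(1 − ρ) + 1 = 1.4.
- Ratio: 1.4/0.4 = 3.5. At ρ = 0.6 it is 1.8/0.8 = 2.25, and at ρ = 0.9 it is 1.2/0.2 = 6.0.
- Correlation of change with baseline Vocabulary: −1/√1.4 = −0.85.

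**Global change (15 repeated tests, ρ = 0.8 for each).**
- Independent test changes: 15 × 0.4 = 6.0; with the Vocabulary term, 7.0. The rise is 1/6.0 = 17% in variance, or √(7.0/6.0) = 1.08, about 8% in SD.
- Test changes correlated 0.1 (assumed): 15 × 0.4 + 15 × 14 × 0.1 × 0.4 = 6.0 + 8.4 = 14.4; with the Vocabulary term, 15.4. The rise is 1/14.4 = 7% in variance.
- Correlation of global change with baseline Vocabulary: −1/√7.0 = −0.38 and −1/√15.4 = −0.25 respectively.

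**Chance imbalance.** With 20 controls and 40 per intervention group, the standard error of a difference in mean baseline Vocabulary under simple randomisation is √(1/20 + 1/40) = 0.27 SD. In an unadjusted change score the whole difference passes into the language contrast. If follow-up is instead regressed on the baseline composite, with an assumed Vocabulary–BNT correlation of 0.5, the coefficient on that composite is (0.8 + 0.5)/(2 + 2 × 0.5) = 1.3/3 = 0.43 rather than 1.

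**The case against.** **Baseline-only use may have been intended.** A footnote that singles out one subtest looks deliberate, and no sentence says that follow-up language will be BNT alone. This stands in part: the documents show an unreconciled conflict, not proof that mismatched scores will be computed. But if baseline-only use was meant, Table 3 is wrong as printed.

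**A fuller plan or imputation could settle it.** The article itself fixes both the composite and the schedule, and they disagree, so this is not a detail left to another document. Imputation is offered in the context of drop-outs. Follow-up Vocabulary is absent for everyone, so no observed values exist to model. Carrying baseline forward would force zero change in half of the language domain.

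**All arms are treated alike.** This stands. A reader might infer that the comparison between arms is biased; the documents do not support that, because under randomisation the Vocabulary term contributes zero in expectation to a condition-by-time contrast. Sample z-scores also average zero at baseline, so dropping the term shifts no overall mean.

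**Imbalance need not pass through in full.** This stands too. Step (c) considers controlling for baseline, randomisation is stratified by education, and years of education is a preset covariate. The 0.27 SD is therefore an upper figure.

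**The large figures concern a domain outside the primary hypotheses.** This is correct. A reader might carry the 3.5-fold variance or the −0.85 correlation over to the hypothesised outcomes. They apply to language only.

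**Conclusion.** The point holds as an internal contradiction that affects a listed primary domain and, more mildly, the global score in primary hypotheses 1 and 3. As written, language goes from two tests to one and the global score from 16 to 15, so steps (b) and (d) compare unlike scores.

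For language the loss of precision is large under the stated assumptions: 3.5-fold variance of change, with a range of 2.3 to 6.0. For the global score it is modest, about 7% to 17% of change variance depending on how test changes correlate. The built-in negative association with baseline Vocabulary matters for analyses of who changes, such as those under secondary hypothesis 5. It too is much weaker for the global score (about −0.25 to −0.38) than for language. Executive function, memory and attention-speed contain no Vocabulary and are unaffected. The documents do not support a claim that any arm is favoured.

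**What to change.** Remove Vocabulary from the outcome composites in Table 3 and list it as a baseline descriptor or covariate. Add one sentence under Primary Outcomes or Statistical Analyses saying that the language and global scores are built at both visits from the same repeated tests: BNT for language, and 15 tests in all for the global score.

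The cost is one table edit and one sentence, with no new data collection. The small downside, which should be stated, is that language then rests on a single 15-item test.

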### Randomization

Participants are randomly assigned to the groups stratified by sex, age, and education. The allocation sequence consists of a random list of these variables all combined and was generated by a statistician. The intervention staff is responsible for the allocation and informs participants at the first intervention visit. Assessors are blinded to the sequence and the group assignment of the participants. Blinding will only be broken for medical reasons.

### Intervention

The intervention consists of a 3 months program, 5 days per week in sessions of 45 min. At baseline all participants receive oral and written information about their specific intervention, an actimeter with brief instructions, and a follow-up diary to monitor the intervention. They are also asked to register hours of sleep during the first and last week of the intervention. AE and COMB groups are also trained to monitor the intensity of their activity using the Borg Rating of Perceived Exertion Scale (BRPES) (Borg, 1982) while CCT and COMB conditions are informed about the computer program. A follow-up calendar is also created to determine adherence and any interfering events. All participants receive phone calls every 2 weeks, a mid-point intervention visit after 6 weeks and a final visit (Table 2).

#### Computerized Cognitive Intervention (CCT)

The intervention program consists of a set of multi-domain cognitive tasks targeting executive function, visual and verbal memory and sustained, divided and selective attention using a computerized telerehabilitation platform called Guttmann NeuroPersonal Trainer^®^ (GNPT^®^, Spain; Solana et al., 2014; Solana et al., 2015). The cognitive functions trained are assessed with the battery of neuropsychological tests. However, the specific training tasks differ from the task performed in the assessment. GNPT includes a variety of exercises designed by neuropsychologist based on cognitive paradigms. The GNPT^®^ platform calculates an individual profile based on age, educational level and the results of the neuropsychological assessment. The demand of the tasks is adjusted according to the performance of previous activities, which allows the software to design a new activity plan adapted to the participant level in each cognitive domain. Training is done individually at home for 45 min per session. Participants without access to a personal computer or Internet can perform the intervention in the health care center. The software records the numbers of sessions and performance in activities automatically.

#### Aerobic Exercise (AE)

The training program is based on international guidelines of physical exercise (World Health Organization [WHO], 2010). Participants are instructed to walk briskly in one continuous bout (45 min for 5 days, 225 min per week); intensity and duration are initiated in a stepwise manner in order to reduce the possibility of injury. The first week they must walk 30 min at 9–10 on the BRPES (Borg, 1982) considered light intensity. Time is increased to 45 min with the same intensity during the second week. During the rest of the program (10 weeks), they maintain the 45 min and increase the intensity of the activity to a moderate-high effort that corresponds with 12–14 in the same scale. Subjects are trained to use the BRPES (Borg, 1982) and to record this intensity and frequency of activity in a diary.

#### Combined Training (COMB)

This group receives both the CCT and the AE intervention. They follow the same previously described instructions for each condition. Participants can organize both tasks at their convenience, always applied in a single continuous bout of 45 min each at any moment of the day. This results in 90 min of daily activity, 5 times per week. We did not set any restriction about the order of the tasks during the day or time-point at which they had to be applied.

#### Control Group

Participants in the control group are on the waiting list for 3 months and are asked to keep their normal lifestyle. Once the control condition is finished, they have the option to start one of the interventions (CCT, AE, or COMB). Data of this optional activity will not be included in the trial as they are not considered participants during this period.

### Safety Considerations

In order to anticipate, prevent and answer medical or personal issues of the participants, several considerations will be taken into account. First, all the assessments are reviewed by the corresponding health professional before randomization to ensure safety during the intervention. Abnormalities identified are reported and these participants are rerouted to the corresponding healthcare service. Participants receive reports of all the assessments. Instructions for each intervention include healthy advice to prevent injuries. Participants can also contact the intervention staff for any problems or pain that they may experience. Adverse events occurring during the intervention are monitored in a diary and sent to a physician in case of medical incident. Participants will be excluded from the trial based on medical recommendation.

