### Assessments

Potential participants are screened by phone and an on-site personal interview; if eligible, informed written consent is obtained. Assessments are conducted in a clinical environment and organized into three appointments that take place at baseline – within 2 weeks prior to the start of the intervention, and again at 3 months within 2 weeks after the completion of the intervention (Table 2). (1) Medical assessment (30 min): review of medical history and current health status including cardiovascular risk factors and blood extraction between 8 and 9:30 AM following an overnight fast. (2) Cognitive assessment and physical status (2.5 h): administration of a battery of neuropsychological tests, psychological health, subjective performance, daily activities and PA questionnaires and a treadmill fitness test. In order to control the effects of acute exercise, participants are advised not to exercise prior to all appointments and cognitive tests are conducted before the CRF test. (3) Magnetic Resonance Imaging (MRI) scans (45 min): administration of a neuroimaging protocol to acquire structural and functional data of the brain. All assessments are carried out in two primary care centers except MRI scans that are performed in the Hospital Germans Trias i Pujol. All subjects receive an actimeter the first and last week of intervention to track their daily activity and determine if participants meet the intervention protocol. The same team of psychologists, which administers cognitive tests, and nurses, who collect general health data, follow the protocol in all the centers.

**TABLE 2 T2:** Assessments.

	**Enrollment and screening**		**Baseline assessments** **(within 2 weeks prior to the start of the intervention)**			**Intervention**			**Post-intervention assessments** **(within 2 weeks after the completion of the intervention)**		
				
	**Telephone screening**	**Visit 1: Screening**	**Visit 2: Baseline assessment**	**Visit 3: Baseline assessment**	**Visit 4: Baseline assessment**	**Visit 5: Initial intervention**	**Visit 6: Mid-intervention**	**Visit 7: Final intervention**	**Visit 8: Post-intervention assessment**	**Visit 9: Post-intervention assessment**	**Visit 10: Post-intervention assessment**
First review of criteria	X										
Montreal Cognitive Assessment 5-min (MoCA 5-min)	X										
Information of study	X	X									
Exhaustive review of criteria		X									
Informed consent form		X									

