##### Aerobic fitness

CRF is assessed by the Rockport 1 mile walk test. Participants are instructed to walk on a treadmill for 1 mile adjusting their speed in order to be as fast as possible without running (Technogym^®^, Italy). Maximal aerobic capacity (VO2 max) will be estimated with the linear regression reported by Kline et al. (1987). CRF estimation is a well-known measure of cardiovascular health. We expect to describe the relationship between CRF and the physiological blood measures as well as how change in CRF relate to brain and cognitive outcomes.

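### The stated adverse-event window leaves out both treadmill tests and everything after training ends, and the two-weekly calls are not described as asking about adverse events

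*Protocol article*

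**What the plan says.** The Safety Considerations section sets both the period and the record for adverse events: "Adverse events occurring during the intervention are monitored in a diary and sent to a physician in case of medical incident". It adds that participants may contact the intervention staff about problems or pain. Table 2 marks the follow-up diary at Visits 5, 6 and 7, and its footnote 4 says who fills it in: "Participants record the diary every day during the intervention".

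The Assessments section places the outcome visits on either side of that period: "within 2 weeks prior to the start of the intervention, and again at 3 months within 2 weeks after the completion". Table 2 puts the fitness test at Visits 3 and 9. The Aerobic fitness section describes the test: "Participants are instructed to walk on a treadmill for 1 mile adjusting their speed in order to be as fast as possible without running".

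The Intervention section gives every participant a call every two weeks, a visit at six weeks and a final visit, and a calendar for adherence and interfering events. Footnote 2 of Table 2, attached to the row of follow-up adherence questions, describes the calls: "This information is also collected in phone calls every 2 weeks between visits". At the end of the Neuroimaging section, the article promises a description of the types of adverse event among the follow-up parameters.

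**The concern.** A harms description can be no better than the window and the method of asking behind it. Here both are stated, and neither fits the trial's own schedule well.

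The window covers training but not the assessments, although physically inactive adults aged 50 to 70 walk a mile at their fastest pace there, twice. An event at a test, or one that begins between the end of training and Visit 10, has no stated place to be recorded.

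The method is a diary that the participant keeps, plus contact that the participant starts. The diary is issued to monitor the intervention, and the advice on preventing injury comes with the instructions for each intervention. Waiting-list controls are asked to carry on as normal. Controls therefore have less prompting to note an event than participants in the active arms, and a comparison of event types between arms could partly reflect who was prompted.

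**Working it through.** No sample size or power figure is involved. The check sets the stated rule against the schedule.

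**Window**

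- Table 2 treats the intervention as its own block, Visits 5 to 7. Baseline (Visits 2 to 4) and post-intervention (Visits 8 to 10) are separate blocks.
- The diary, the only record that the safety section names for adverse events, is marked at Visits 5, 6 and 7.
- Medical assessment and blood sampling are at Visits 2 and 8, the treadmill test at Visits 3 and 9, and MRI at Visits 4 and 10.
- Assessment visits inside the stated window: 0 of 6. Treadmill tests inside it: 0 of 2.
- An event that starts during the last training weeks is inside the window, since the diary and follow-up questions run to Visit 7. One that starts after training ends is outside it.

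**Method of asking**

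| Route | Stated purpose | Described as asking about adverse events? |
|---|---|---|
| Daily diary | Monitoring the intervention; named for adverse events in the safety section | Yes, but self-kept |
| Two-weekly calls | Adherence questions (Table 2, footnote 2) | No |
| Visits 6 and 7 | Adherence questions, diary | Only through the diary |
| Follow-up calendar | Adherence and interfering events | Not as such; an event that disrupts training might appear |
| Check of diaries against calls (Data Quality) | Intervention parameters | No |
| Contact with intervention staff | Problems or pain | Yes, if the participant starts it |
| General health status, Visit 8 | Medical assessment | Not as such |

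The planned gap between staff contacts is about two weeks, so contact is frequent enough. What is missing is a statement that any scheduled contact asks about adverse events in the same way in every arm.

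**The case against.** The strongest reply has four parts.

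1. **Staff contact is frequent.** A reader might infer that a diary entry can go unseen by staff until the six-week visit, or that the diary is the only route. The documents support neither. All participants are called every two weeks, a calendar notes interfering events, and participants can raise a problem with staff whenever they wish. The safety text does not say that the diary is the sole channel. This part of the reply stands.

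2. **The tests are attended.** The Assessments section says: "Assessments are conducted in a clinical environment". An event during a test would probably be seen, and baseline assessments are reviewed by a health professional before randomization. This lowers the weight of the point. It does not answer it, because seeing an event is not recording it, and symptoms that begin after the participant leaves are not seen. Events at the baseline test cannot inform a comparison between arms, but those after training can.

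3. **The diary is daily and goes to everyone.** That is structured recording, and fuller reporting in the active arms is not shown by any figure. This is fair, so the difference between arms is stated here only as possible.

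4. **The article condenses a fuller protocol.** That would excuse silence on forms and call scripts. Here, however, the article states a window and a record, and the stated window does not match the schedule printed with it. The call content is the weaker half of the point for this reason, since a script in the full protocol may already ask about adverse events.

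**Conclusion.** The point holds as an inexpensive improvement of modest weight. As worded, the window omits both treadmill tests, the other assessment procedures and events with onset after training ends. No scheduled call is described as asking about adverse events. This rests on a literal reading of the safety section and on the article alone.

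Two further inferences are tempting and should not be drawn.

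- The assessment windows could be turned into a share of participation: 2 + 2 = 4 weeks against 1 + 1 + 10 = 12 weeks of training gives 4/16 = 25%. Both windows are maxima, half of that time precedes the intervention, and calendar time is not risk. The figure does not measure harm.
- It could be argued that an early event would pass unread through the rise in walking intensity after week 2. A call is already due at about that time and the contact route is open, so the documents do not support this.

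**What to change.** Amend the Safety Considerations section and Table 2 as follows.

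- **Window:** record adverse events from signed consent (Visit 1) to the last post-intervention assessment (Visit 10), including those during or after the treadmill tests.
- **Question:** have intervention staff ask one open adverse-event question, worded identically in all four arms including controls, at the existing two-weekly calls and at Visits 6 and 7. Keeping it with intervention staff protects the blinding of outcome assessors.
- **Reporting:** present events by period (before randomization, intervention, after intervention), so that baseline-test events are not mixed into the comparison of arms.

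The cost is a change of wording, one row in Table 2 and one question on contacts already planned. No visits or staff are added. The downside is more minor events to record. If follow-up has already finished, the trial report should state the window used and how events were elicited.
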